In the last substep of phase 1, the provisional English version of the SCSE-OAC will be in parallel translated and cross-culturally adapted for each native-speaking country involved in the study (ie, Italian). Therefore, an independent group of bilingual experts will be involved in an iterative forward-backward translation process to ensure that the final version of the scale will be conceptually and linguistically correct and understandable to people of all levels of education by being culturally acceptable. Brislin’s translation procedure will be followed [24]. More specifically, 2 expert bilinguals who are native speakers of the target language will translate the English version of the SCSE-OAC into the Italian language, and a third expert will review the 2 translations to achieve the best possible reconciled translation. After that, another 2 bilingual experts who are native speakers of the target language with fluency in English will be involved in the back-translation of the previously reconciled translation to the original language (ie, Italian back to the English language). The results of all 3 tasks (translation, reconciliation, and back-translation) should be forwarded to a permanent panel of experts or translation coordinator to review the process. As a result of the translation process, 2 translated versions of SCSE-OAC will be available (1) SCSE-OAC for the Italian-speaking patients’ group and (2) SCSE-OAC for English-speaking patients’ group. At the end of this translation process, a pilot test will be performed to assess the readability and comprehensibility of the items for each native-speaking group (10-15 patients). Therefore, each patient group will be asked to fulfill the preliminary translated version of SCSE-OAC and highlight any items that are not clear to them. All comments and suggestions will be taken into account. This phase is anticipated to end in December 2024.

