### Phase 2: Validation

This second phase (ie, validation phase) aims to define the construct intended to be measured, providing evidence of psychometrics validity for each translated version of SCSE-OAC. Two main substeps will be performed (1) content and face validity and (2) construct validity.

According to the COSMIN guideline, the content validity of the scale will be assessed based on the key criteria of relevance, comprehensiveness, and comprehensibility. In other words, each item will be analyzed by patients and health care professionals for content, meaning, wording, and format. As per the relevance criteria, we will ask to judge the items’ relevance for the construct of interest (ie, SCSE) on a 4-point Likert scale (1=not relevant, 2=somewhat relevant, 3=quite relevant, and 4=highly relevant), with the following question

Please evaluate the relevance of the following self-care behaviors in managing your oral anticoagulation medication. Which behaviors do you find relevant to your daily life with OAC treatment?

Content validity index (CVI) will be computed at the item and overall scale (ie, I-CVIs and S-CVI), considering a critical threshold value equal to 0.70 for I-CVIs and 0.80 for S-CVI. For each native-speaking country, a minimum of 15 patients will be enrolled to participate in the study.

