The patients’ eligibility criteria will be adult outpatients (18 years of age or older) with ongoing treatment with OAC at the time of the investigation, with a primary clinical indication for long-term OAC for NVAF, treated for at least 3 months, and who are willing to participate in the study. Instead, patients with cognitive decline (ie, Six Item Screener Test with lower than 4 points) will be excluded. Likewise, a convenience sample of 10 voluntary professionals from all relevant disciplines (ie, physician, nurse, and pharmacist) with documented clinical experiences in OAC for at least 1 year will be involved. Sociodemographic and professional variables will be considered to provide a sample description. Finally, an open-ended question will be included to assess the comprehensive and comprehensibility criteria. More specifically, participants will be asked to evaluate whether the items together comprehensively cover the construct of interest and if the population of interest clearly understands the items and response options to evaluate the face validity. The responses will be systematically analyzed, coded, and compared through a qualitative content analysis approach. Data collection will be done through an e-survey.

Following the achievement of content and face validity, 3 forms of validity will be tested—structural, cross-cultural, and criterion validity. As per the structural validity, we will assess the dimensionality of the construct to be measured (ie, SCSE) by factor analysis. However, no clear hypotheses about the underlying dimensions of the construct in the OAC population are available. Therefore, a 2-fold cross-validation will be performed for each language group, using explorative factor analysis (EFA) to explore relationships between observed variables and underlying factors and identify the most plausible psychometric structure and confirmatory factor analysis (CFA) to confirm the most plausible structure derived from EFA. More specifically, the overall sample for each language group will be randomly resampled to generate a subsample A for performing EFA (roughly 50% of the original sample) and subsample B for performing a CFA using the most plausible psychometric structure derived from EFA (using the second 50% of the original sample).

### Sample Size for Phase 2

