### Study Procedures for Cross-Sectional Data Collections

The 2 data collection rounds required for achieving construct validity will be performed using an e-survey or paper form based on patients’ preferences. E-survey is a more accessible and practical approach to gathering data from the desired group using a web survey link. The paper form will be delivered to patients in OAC who will prefer this approach. Considering that some patients could be older, the paper form could overcome the possible challenges that they could have in using an e-survey approach. A preidentified health care professional will oversee patients’ enrollment, get informed consent, and perform data management and monitoring. Each obtained paper form or electronically collected data will be registered (or transferred in the case of data collected via SurveyMonkey [SurveyMonkey Inc]) in REDCap (Research Electronic Data Capture) software (Vanderbilt University; ie, electronic case-report forms). REDCap works as a web-based repository of the data collected. Both SurveyMonkey and REDCap are compliant with the European General Data Protection Regulation.

### Eligibility Criteria for Phase 2

Inclusion criteria for participation in the study are (1) the patients must be aged 18 years or older, (2) have a confirmed diagnosis of NVAF, (3) be outpatients, and (4) have been receiving any OAC for at least 3 months before enrollment. Additionally, patients must provide informed consent. Exclusion criteria are those who have been treated with OAC for a brief period and are not on treatment anymore (ie, less than 3 months), patients with serious comorbidities (ie, Charlson Comorbidity Index, CCI >4), patients who have suspended OAC for surgery in the last 3 months, and those with cognitive impairment (assessed using a 6-item screener <4). Furthermore, a core set of sociodemographic and clinical variables will be collected to comprehensively describe the study sample.

### Measurements for Phase 2

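### The phase 2 content- and face-validity step names only an e-survey, so its small patient panel may under-represent patients who will later complete the scale on paper

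*Protocol article*

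**What the plan says.** The Protocol article describes the content- and face-validity step under Phase 2: Validation. Patients and professionals rate each item's relevance on a 4-point scale. The ratings give the item-level and scale-level content validity indices (I-CVI and S-CVI), with thresholds of 0.70 and 0.80. On the patient side, "For each native-speaking country, a minimum of 15 patients will be enrolled to participate in the study". For the other two criteria, "an open-ended question will be included to assess the comprehensive and comprehensibility criteria", and participants judge "if the population of interest clearly understands the items and response options to evaluate the face validity". The description of the step ends with the mode: "Data collection will be done through an e-survey". No paper route is named.

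For the next step, the section Study Procedures for Cross-Sectional Data Collections states: "The 2 data collection rounds required for achieving construct validity will be performed using an e-survey or paper form based on patients’ preferences". It explains that some patients could be older and that "the paper form could overcome the possible challenges that they could have in using an e-survey approach".

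The Methods part of the Abstract mentions both modes for the study as a whole, without assigning either to a phase.

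**The concern.** The protocol recognises that some of its target patients may not manage an e-survey, and it provides paper for them when the scale is factor-analysed. It does not provide paper when the items are judged. If patients who would choose paper do not take part online, the judging panel differs systematically from the population that goes on to complete the scale.

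Three things are at stake. The I-CVI and S-CVI would reflect the relevance ratings of online responders. Comments on clarity and missing content would come from the same group. And although items are to be examined for format as well as wording, the paper layout would reach the construct-validity rounds without any patient having reviewed it in this step. The section Sample Size for Phase 2 takes the scale version, and hence the number of patients required, from this step, so its output carries forward.

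**Working it through.** The article contains no figure to reproduce on this point. The check is a comparison of the mode stated for each step that uses patient input.

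| Step | Section | Patients | Mode stated | Feeds I-CVI/S-CVI? |
|---|---|---|---|---|
| Focus groups | Phase 1: Conceptualization | start with 5, more until saturation, in each country | moderated discussion | No |
| Readability pilot | Phase 1: Conceptualization | 10-15 per language group | not stated | No |
| Content and face validity | Phase 2: Validation | at least 15 per country | e-survey | Yes |
| Construct-validity rounds | Study Procedures for Cross-Sectional Data Collections | 100 per language group if the scale has 10 items | e-survey or paper, by preference | No |

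**Is the population different?** No. Both phase 2 steps take adult outpatients with NVAF treated for at least 3 months, with the same cognitive screen. The content-validity step has no upper age limit, and the comorbidity exclusion is listed only for the later rounds. Nothing suggests that its patients would cope better with an e-survey.

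**Does the Abstract settle the mode?** No. Its mention of both modes is satisfied by the construct-validity rounds alone and does not override the specific sentence in Phase 2: Validation.

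**How sensitive is a panel of this size?** Assume that the patient panel is scored on its own at the minimum of 15. One rater moves an I-CVI by 1/15 = 0.067. The 0.70 threshold corresponds to 0.70 × 15 = 10.5 raters, so 11 endorsements pass (11/15 = 0.733) and 10 fail (10/15 = 0.667). The make-up of the panel can therefore matter by one or two patients for a borderline item.

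**How large a difference would change a clear decision?** This concerns relevance only, since the I-CVI is built from relevance ratings. All inputs are assumptions: a share *p* of patients would use paper and is absent from the e-survey, online patients endorse an item at 0.90, and paper patients endorse it at *e*. Endorsement in the whole population is 0.90(1 − *p*) + *p·e*, which falls below 0.70 when *e* < 0.90 − 0.20/*p*.

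- *p* = 0.20: *e* < 0.90 − 1.00 = −0.10, which is impossible.
- *p* = 0.40: *e* < 0.90 − 0.50 = 0.40. For instance, *e* = 0.50 gives 0.54 + 0.20 = 0.74 (still retained), and *e* = 0.30 gives 0.54 + 0.12 = 0.66 (not retained).
- *p* = 0.60: *e* < 0.90 − 0.333 = 0.567.

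So an item rated well online would be wrongly kept only if paper users were numerous and rated it very differently. The article supports no particular value of *p* or *e*. These figures show what would be needed and do not estimate an effect.

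**The case against.** The strongest reply is that patients are heard by other routes. The focus groups are spoken, run in both countries and continue to saturation. They supply challenges and help shape item wording. The pilot has patients complete the scale and flag unclear items, all comments are considered, and it is not confined to an e-survey. Later, the Data Analysis section keeps only items loading above .40, in a sample that includes paper users. A condensed article may also leave help with completing the survey to the full protocol.

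Much of this stands, and it limits the point. It does not remove it. Neither phase 1 activity contributes to the I-CVI or S-CVI. The pilot's mode is unknown. Factor analysis can drop an item but cannot reword one or add a missing behavior. And the article does more than stay silent: it states one mode here and a choice of modes for the next step.

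A reader might go further in three ways that the document does not support.

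- One might infer that comprehensibility is tested in those least likely to have trouble. The article says only that older patients could find the e-survey hard, and difficulty with a web form is not difficulty understanding an item.
- One might infer that the aim of a scale "understandable to people of all levels of education" is tested only in a selected group. That aim is set for the translation process, and the readability pilot follows it directly.
- One might infer that unclear items would pass through an inflated I-CVI. The I-CVI measures relevance; clarity is assessed through the open-ended question.

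**Conclusion.** The inconsistency is real and modest. The protocol gives a reason for offering paper, applies it to the construct-validity rounds, and does not apply it to the preceding step, where the same kind of patient judges the items. The panel may under-represent patients who will later use paper, and no patient review of the paper format is planned in that step.

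This rests on two assumptions: that the single mode named in Phase 2: Validation is meant literally, and that some patients who prefer paper would not respond online. The size of the effect cannot be calculated from the article. For items that online patients rate clearly relevant, a changed decision would need a large gap between modes; borderline items in a panel of 15 are more exposed. The point justifies a change because the remedy is cheap and comes before all later validation, and not because serious bias has been shown.

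**What to change.** In Phase 2: Validation, replace the sentence on mode with the rule already used for the construct-validity rounds: patients may answer the content- and face-validity questions by e-survey or on paper, as they prefer, and the mode used is recorded. Professionals stay on the e-survey. It would also help to state the mode of the phase 1 readability pilot.

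The cost is small. At the minimum panel size, at most 15 forms per country would need printing and keying, and the route from paper into REDCap is already planned. The downside is slightly slower collection. With so few patients, any comparison of ratings or comments by mode would be descriptive only.

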In the field of factor analysis, the sample size estimation for allowing researchers to perform factor analysis properly is based on a rule of thumb supported by the Monte Carlo simulation study of enrolling 10 patients per item and per language group [25]. As a result, the final required sample size will be based on the version of the SCSE-OAM derived from the content validity phase because it depends on the number of items encompassed in the scale. Considering previous similar research in patients with heart failure, 10 items were developed for measuring SCSE for adults with heart failure. We hypothesized a similar number of items. In this case, 100 patients per language group will be necessary for EFA and subsequently for CFA.

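### The 100 patients per language group are not reconciled with the 50/50 EFA/CFA split: either each analysis has 5 patients per item, or the requirement is 200 per group, which is stated nowhere

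*Protocol article*

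**What the plan says.** Three neighbouring parts of the protocol article's Methods bear on this.

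- **Sample Size for Phase 2.** The rule of thumb is "enrolling 10 patients per item and per language group". The item count is borrowed from a heart failure scale: "10 items were developed for measuring SCSE for adults with heart failure. We hypothesized a similar number of items". The conclusion is "In this case, 100 patients per language group will be necessary for EFA and subsequently for CFA". The figure is provisional, since "the final required sample size will be based on the version of the SCSE-OAM derived from the content validity phase".
- **Phase 2: Validation.** For the two-fold cross-validation, "the overall sample for each language group will be randomly resampled to generate a subsample A for performing EFA", with roughly half of the patients in it. The CFA is run on subsample B, "using the second 50% of the original sample".
- **Study Procedures for Cross-Sectional Data Collections.** This section opens with "The 2 data collection rounds required for achieving construct validity". It does not say what each round is for or how many patients each should supply.

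No total of 200 per language group, or 400 overall, appears anywhere. Nor does the article say that 100 is the number before the split.

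**The concern.** The rule and the split are expressed in the same unit, the language group. The rule yields 100 for that group, with no factor for there being two analyses, and the split then halves the group. Taken together, the two sections deliver half the ratio that the sample-size section presents as the basis for doing factor analysis properly.

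This is the only sample-size justification for structural validity, which is central to the primary aim. The structure found in the EFA is carried into the CFA for both languages, and the invariance testing follows from there. The article says that no clear hypotheses exist about the dimensions of the construct, so there is no prior model against which to check an unstable EFA solution. A site that reads only the sample-size section could reasonably stop at 100 per language. If 200 was intended, recruitment would end at half the requirement.

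**Working it through.** **Inputs.** 10 patients per item per language group, 10 assumed items and 100 patients per language group (Sample Size for Phase 2). A split of about 0.5 to each analysis (Phase 2: Validation). Two language groups.

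**Step 1: reproduce the stated figure.** N = patients per item × items = 10 × 10 = 100 per language group. This matches. The rule is used up at this point; no factor of 2 for two analyses enters.

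**Step 2: apply the split under each reading.**

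| | 100 is the group total | 100 is for each analysis |
|---|---|---|
| Patients per analysis | 100 × 0.5 = 50 | 100 |
| Patients per item in each analysis | 50 / 10 = 5 | 100 / 10 = 10 |
| Total per language group | 100 | 100 / 0.5 = 200 |
| Total, both groups | 200 | 400 |

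A half-sample of 50 meets the rule of 10 per item only for a scale of up to 50 / 10 = 5 items.

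**Step 3: does the provisional item count matter?** With k items the rule gives 10k per group, and each half then has 5k, so the ratio is 5k / k = 5 for any k. For 8, 10, 12 and 15 items the rule gives 80, 100, 120 and 150. If each half is to meet it, the group totals are 160, 200, 240 and 300.

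**Step 4: illustrations of the loss from 100 to 50 per analysis.** These rest on assumptions that the article does not make.

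- *CFA.* Take a correctly specified one-factor, 10-item model with df = 35 and the asymptotic chi-square distribution. The chance of missing an RMSEA limit c is P(χ²₃₅ > 35 + c² × 35 × (N − 1)). For c = .05 the cut is 39.29 at N = 50 and 43.66 at N = 100, giving 28% and 15%. For c = .08 the chances are about 10% and 1%.
- *EFA.* Simulations used principal-axis factoring, promax rotation, parallel analysis by the mean-eigenvalue rule and loadings above .40. The table shows the percentage of samples in which the assumed structure was recovered; ranges cover separate runs or eigenvalue methods.

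| Assumed structure | n = 50 | n = 100 |
|---|---|---|
| Three factors (4/3/3), loadings 0.7, correlation 0.3 | 55–64% | 91–94% |
| Three factors, loadings 0.8, correlation 0.5, unreduced eigenvalues | 27–28% | 51–58% |
| The same, reduced (common-factor) eigenvalues | 89% | 99.5% |
| One factor, loadings 0.7 | 97% | 100% |
| One factor, loadings 0.6 | 61–68% | 87–92% |

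The article does not fix the number of factors or say which eigenvalues the parallel analysis uses, so no row can be called the expected loss.

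**The case against.** The strongest reply is that the sample-size sentence can be read as 100 for the EFA and then another 100 for the CFA, and that the two data collection rounds are compatible with this. On that reading every analysis has 10 patients per item and nothing falls short. This stands as far as it goes. A reader might infer that 100 per group cannot meet the rule, or that each analysis will certainly have 50 patients. The text does not support that certainty, and the product 10 × 10 = 100 is itself correct. But the alternative reading does not make the protocol complete: it requires 200 per language group, which is never printed. Two separate rounds would also not be a random division of one overall sample.

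A second reply is that the number is provisional and must be recomputed once the items are settled. That is true of the number but not of the ratio. If the rule sets the whole group, the ratio is 5 per item at any item count.

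A third is that the harm depends on the scenario. This stands in full. With one strong factor, 50 patients nearly always suffice, and the lowest recovery figures depend largely on the eigenvalue method. The RMSEA limit of .05 marks the article's good-fit band and is not a declared pass mark; .08 is also listed. A reader might infer from the adverse scenarios that the EFA is likely to fail. The documents give no factor structure from which to say so.

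Finally, the rounds cannot be treated as a third, competing sample size. The article gives no number for them and assigns neither to EFA or CFA.

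**Conclusion.** The point holds as an unreconciled sample size that needs correcting. The stated size, rule and split do not determine one enrolment target. On the plainer reading, each analysis has about 50 patients and 5 per item, half the ratio relied on. On the other, the requirement is 200 per language group and 400 overall, twice the only figure printed. The factor of two follows from the article's own figures and does not depend on the final item count; the absolute numbers assume 10 items and an even split. What this costs in accuracy of the EFA and CFA cannot be fixed from the document. The simulated losses show only that it can range from slight to substantial.

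**What to change.** In Sample Size for Phase 2, state the total per language group before the split and the resulting ratio in each analysis. Either of two statements would be coherent:

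1. 20 patients per item per language group, so that each half meets 10 per item. At 10 items this is 200 per group and 400 in total.
2. 100 per language group at 10 items, with the ratio restated as 5 per item in each half and the lower precision of both the EFA and the CFA acknowledged.

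Then make Phase 2: Validation, Sample Size for Phase 2 and Study Procedures for Cross-Sectional Data Collections agree on whether EFA and CFA use one randomly split sample or two rounds, and say what the rounds are.

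The text change is a few sentences and should be made before Phase 2 enrolment closes. Option 1 means 100 more patients per language group only if 100 was the intended total; otherwise it costs nothing beyond the wording. Option 2 needs no extra patients, but the stated justification becomes weaker.
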